### Secondary outcome measures

#### Gait

Gait and posture will be assessed pre- and post-intervention during a two-minute continuous walk using an instrumented walkway and a small, lightweight, sensor worn on the lower back (AX6, Axivity, York, UK; sampling frequency = 100 Hz, gravitational acceleration =  ± 8 g, and gyroscope full-scale range (dps) = 2000, attached using double sided tape and secured in place using hypafix [BNS Medical Limited, Hull, UK]). The sensor is an inertial measurement unit comprising a tri-axial accelerometer and gyroscope. Participants will walk at a comfortable walking pace around a 25 m circuit inclusive of a 6.1 × 0.6 m instrumented walkway (ProtoKinetics LLC, Havertown, Pennsylvania, 120 Hz). The analysis will focus on dopa-resistant characteristics; namely, step time variability and step length variability [4, 13, 49], and other discrete characteristics representing five domains according to an a priori model of gait in PwP (see Table 2 for details) [50].

**Table 2 Tab2:** Description of the validated model of gait in PwP as described by Lord and colleagues [50]

	Gait domain	Description
Validated model of gait in PwP	Pace	The pace domain is captured by characteristics such as step velocity and step length
	Rhythm	The rhythm domain presents the temporal regulation of gait and the timing of steps such as step time, swing time and stance time
	Variability	The variability domain represents the differences from one step to the next. This domain contains variability gait characteristics such as the variability of step length, step time and stance time
	Asymmetry	The asymmetry domain represents the temporal differences between left and right steps and includes gait characteristics measuring the asymmetry of swing time, step time and stance time
	Postural control	The postural control domain represents the ability to maintain balance during walking with gait characteristics including mean step width

### Ambulatory activity

Ambulatory activity will be measured in the real-world using a body-worn sensor on the lower back (same sensor as used in the laboratory assessment, attached using hydrogel patch [Amgel Technologies, USA] and secured in place using hypafix). Participants will be asked to wear the sensor for seven consecutive days to provide free-living data in terms of gait activity. Outcome measures will be in accordance with published work [51, 52]. Description of these measures, which can be broadly categorised into three domains including volume, pattern, and variability (macro gait characteristics), is described briefly in Table 3.

**Table 3 Tab3:** Description of macro (behavioural) gait characteristics quantified from wearable sensors worn for seven days

	Category	Description
Macro (behavioural) gait characteristics	Volume	Volumetric outcomes describe the quantity or amount of activity levels. From this total walking time, steps per day and bouts per day will be reported
	Pattern	Pattern outcomes describe the type of walking behaviour and will include descriptors such as mean bout length (based on ambulatory bouts) and the non-linear descriptor *alpha*. This variable captures the distribution of ambulatory bouts and is the ratio of short to long bouts
	Variability	The variability outcome describes the within-subject variation of bout length capturing walking activity. Higher variability is interpreted to indicate more varied walking patterns whereas lower variability indicates more repetitive and habitual levels of activity

Previous work from our group indicates the sensor is well tolerated [51, 53, 54]. Macro gait characteristics will be measured following baseline (t_1_), the 12-week treatment phase (t_4_) and the 24-week assessment (t_5_).

### Cognition

Attention and fluctuating attention will be measured using a computerised battery by assessing mean reaction time during simple reaction time (SRT), choice reaction time (CRT) and digit vigilance (DV) tests (examples of these tests are depicted in Fig. 2) [55, 56]. Power of attention (PoA) will be computed as a marker of attention and is the composite score of mean reaction time from all three tests reported in milliseconds. Fluctuating attention will be determined by the coefficient of variance (CoV) of the three tests. Also, digit vigilance accuracy will be reported as the percentage of correct targets detected.

**Fig. 2 Fig2:**
[figure not shown]
The figure illustrates the three cognitive assessments: simple reaction time task (**A**), choice reaction time task (**B**) and Digit vigilance task (**C**) collectively measuring attention and fluctuating attention. Hand icon represents the participant’s hand responding to the stimuli displayed on the computer screen. For SRT and DV the dominant hand is used

Executive and memory functions will be evaluated using the computerised Cambridge Neuropsychological Test Automated Battery (CANTAB) [57]. Executive function will be assessed using the One Touch Stockings of Cambridge (OTS) and Paired Associates Learning (PAL) will be used to assess memory. The use of these two assessments is informed by previous research [56, 58]. The Trail Making Test (TMT) parts A and B will be used to assess attention and executive function, respectively.

### Falls

Consistent with the recommendations of the Prevention of Falls Network Europe group falls will be defined as “an unexpected event in which the participant comes to rest on the ground, floor, or lower level” [59]. These will be recorded prospectively using standardised falls diaries, sent out on a monthly basis with a pre-paid envelope and regular telephone calls from a study team member, to verify the information [60, 61].

### Cholinergic peripheral plasma markers

Approximately 14 ml of whole blood will be taken from participants pre- and post-intervention. Samples will be used to measure cholinergic peripheral markers in plasma. Metabolomic analysis of blood plasma concentrations of protein elements of the cholinergic metabolic pathway will be completed by external collaborators. Plasma will be analysed, and protein elements involved in the cholinergic (Cho) metabolic pathway will be identified and quantified. Assays will be validated for specificity, linearity, accuracy, precision, recovery, and stability according to FDA bio-analytical method validation guidelines [62].

### Focus group

The primary goal of our focus group, which will be held with a subset of participants towards the end of the trial, will be to co-plan and co-design a future, multi-site nVNS trial in PwP.

### Statistical analysis

The main analyses will be descriptive, to inform the design of a future trial. We will analyse the numbers of eligible patients enrolled, rate of recruitment, compliance with the intervention and completion of study assessments. We will ascertain the completeness and acceptability of nVNS and identify any potential barriers. Qualitative data analysis from the focus group will adopt a thematic approach [63] with NVivo (QSR International Pty Ltd. NVivo) software used as a coding tool. Statistical analyses will be conducted using MATLAB (The MathWorks, Inc., Natick, MA, USA), SPSS (IBM SPSS Statistics for Windows, Armonk, NY: IBM Corp) and/or R (http://www.r-project.org/). The outcome data will be summarised using descriptive statistics, including means (and medians), standard deviations, and interquartile ranges. It is expected that non-parametric statistics (e.g., Friedman test) will be used throughout due to the small number of participants in this study. To establish proof of concept for active nVNS treatment, we will compare the median change scores (post–pre assessment) of gait and cognitive outcomes between groups using Mann–Whitney U tests. An exploratory outcome will be a metabolomic analysis of cholinergic markers in blood plasma. We will explore the effects of concentrations of the various targeted small molecule Cho metabolites (Cho inclusive) in plasma on cognitive functions and discrete gait characteristics.

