**Design:**

This will be an investigator-initiated, single-site, proof-of-concept, double-blind sham-controlled randomised pilot trial in 40 people with PD. Participants will be randomly assigned on a 1:1 ratio to receive either active or sham transcutaneous cervical VNS. All participants will undergo comprehensive cognitive, autonomic and gait assessments during three sessions over 24 weeks, in addition to remote monitoring of ambulatory activity and falls, and exploratory analyses of cholinergic peripheral plasma markers. The primary outcome measure is the safety and tolerability of multi-dose nVNS in PD. Secondary outcomes include improvements in gait, cognition and autonomic function that will be summarised using descriptive statistics.

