### Participants and eligibility criteria

We aim to recruit 40 PwP in total. This study will be used to establish proof-of-concept and feasibility allowing power calculation for a larger definitive clinical trial. Participants will be over 18 years of age but younger than 76 years of either sex and of any racial or ethnic origin. The age cut-off will be used due to the lack of safety data in older or younger participants. All participants will have a diagnosis of PD, as per the UK Brain Bank Criteria [28] and participants may be Hoehn and Yahr stages I to III [29]. All participants must be on stable medication for the preceding month and anticipated over the next three months, able to walk independently without aid for a minimum of two minutes without rest and able to provide informed consent. Our exclusion criteria include:Parkinson’s disease dementia [30] or significant cognitive impairment as determined by a score of < 21 on the Montreal Cognitive Assessment (MoCA);History of stroke, traumatic brain injury, intracranial aneurysm, intracranial haemorrhage, brain tumour or atypical parkinsonian disorder;An unstable medical condition in the last six months or planned surgeries that may involve implants within the next six months;Prescribed centrally acting anticholinergics (e.g., amitriptyline) or cholinesterase inhibitors;Severe orthopaedic or neurological (excluding PD) pathology that will adversely affect gait;Pain at the nVNS treatment site (e.g., dysesthesia, neuralgia, cervicalgia);Previous use of nVNS stimulator device, including previous participation in nVNS research;Women of childbearing potential or who are pregnant or lactating;Active participation in another interventional trial or exposure to an experimental drug or intervention;Lesion (including lymphadenopathy), previous surgery (including carotid endarterectomy or vascular neck surgery) or abnormal anatomy at the treatment site (open wound, rash, infection, swelling, cut, sore, drug patch, surgical scar[s]);Known or suspected severe atherosclerotic cardiovascular disease, severe carotid artery disease (e.g., bruits or history of TIA or stroke), congestive heart failure, known severe coronary artery disease or prior myocardial infarction;Abnormal baseline electrocardiogram (ECG) within the last year (e.g., second or third-degree heart block, prolonged QT interval, atrial fibrillation, atrial flutter, history of ventricular tachycardia or ventricular fibrillation);Uncontrolled high blood pressure (systolic > 160 mmHg, diastolic > 100 mmHg) after 3 measurements within 24 h;Previous unilateral or bilateral vagotomy;Implanted metal cervical spine hardware, other metallic implants or implantable medical devices such as deep brain stimulator, hearing aid implant, pacemaker, implanted cardioverter defibrillator, cranial aneurysm and/or cranial aneurysm clips, history of facial/orbital/metallic fragments, implanted electronic device, neurostimulator, valve replacements/stents, metallic implants/prostheses) near the stimulation site such as a bone plate or bone screw;History of syncope or seizures (within the last 2 years);Patients with active cancer or are in a recent remission of cancer;Clinically significant hypotension, bradycardia, or tachycardia;Insufficient comprehension of the English language.

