### Randomization and blinding

Patients who provide informed consent to participate and fulfil the eligibility criteria will be equally randomised using a covariate-adaptive randomisation process with a minimisation method [32] into two groups to receive either active nVNS or sham nVNS. This is achieved using the variance minimisation procedure recently proposed [33]. Allocation to groups will be stratified by age, sex, global cognition (MoCA scores) and motor severity (scored using the MDS-UPDRS-III). Both patients and researchers performing the assessments and analyses will be blinded to the intervention.

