### Sample size

The purpose of this study is to establish proof of concept and feasibility for a larger clinical trial and the number of participants recruited for this study (*n* = 40) matches that of a recent feasibility trial [36]. This study will therefore establish a proof of concept and allow power calculations for a definitive trial.

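### The proof-of-concept tests on change scores use neither an estimated baseline slope nor the minimisation factors, so the gait and cognition comparison is less precise than the collected data allow

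*Protocol article*

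**What the plan says.** The Statistical analysis section of the Protocol article gives the main analyses a descriptive role: "The main analyses will be descriptive, to inform the design of a future trial". It then names one between-group comparison of efficacy outcomes: "we will compare the median change scores (post–pre assessment) of gait and cognitive outcomes between groups using Mann–Whitney U tests". No covariate is mentioned. The reason given for rank methods is sample size: "It is expected that non-parametric statistics (e.g., Friedman test) will be used throughout due to the small number of participants in this study".

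Randomization and blinding describes minimisation on four factors: "Allocation to groups will be stratified by age, sex, global cognition (MoCA scores) and motor severity (scored using the MDS-UPDRS-III"). Baseline gait and baseline reaction time are not among them, although both are measured at the first visit.

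The target is 40 participants, allocated 1:1. The Sample size section says only that this number "matches that of a recent feasibility trial", and that the trial will allow power calculations for a definitive trial.

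**The concern.** The test, the outcome form and the purpose are all fixed in the article, so this is a stated choice and not a detail left to a fuller document. It has three weaknesses.

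- **Baseline.** If the true pre–post slope is below 1, subtracting the whole baseline over-corrects. Noise is added, and an arm that starts worse by chance tends to look better on change.
- **Minimisation factors.** Allocation is balanced on them, but the test does not use them.
- **Output.** The Mann–Whitney test compares distributions through ranks. It addresses a difference in medians only under extra conditions, such as a pure shift in location. The comparison as worded gives a p-value, whereas planning a definitive trial calls for a between-arm difference with an interval.

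At stake is the precision of the signal that decides whether a larger trial is justified and how large it should be. The reason given, small numbers, does not rule out adjustment: rank-based analysis can also adjust for baseline, and precision matters more when patients are few.

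**Working it through.** **Inputs.** From the article: 40 participants, 1:1, hence 20 per arm; four minimisation factors; an unadjusted test on change. Not given, and so assumed: the correlation rho between baseline and follow-up (0.3 to 0.9), equal SD (sigma) at both times, two-sided alpha 0.05, and the effect sizes below. I read the post assessment as the 12-week visit. The article's figure of 40 cannot be reproduced, because no effect, SD, power or alpha is stated.

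**Variance.** The between-arm contrast has variance proportional to:
- change score: 2(1 − rho)·sigma²
- ANCOVA: (1 − rho²)·sigma²

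The ratio is (1 − rho²) / [2(1 − rho)] = (1 + rho)/2. Estimating one slope costs a factor of about 1 + 1/36 = 1.028.

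**Chance imbalance.** The SD of the baseline difference between arms of 20 is √(2/20) = 0.316 sigma. The change-score contrast moves by (1 − rho) times that difference.

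| rho | ANCOVA/change variance | with penalty | shift from a 1-SD chance imbalance |
|---|---|---|---|
| 0.3 | 0.65 | 0.67 | 0.22 sigma |
| 0.5 | 0.75 | 0.77 | 0.16 sigma |
| 0.7 | 0.85 | 0.87 | 0.09 sigma |
| 0.9 | 0.95 | 0.98 | 0.03 sigma |

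Under normality the Mann–Whitney test loses up to a further 5% (asymptotic efficiency 3/pi = 0.955).

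**Power by simulation.** Settings: 20 per arm, normal data, 3,000 runs, minimisation factors assumed to have no prognostic value.

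| rho, effect | Mann–Whitney on change | ANCOVA, baseline only | ANCOVA, baseline + four factors |
|---|---|---|---|
| 0.5, 0.7 SD | 55% | 69% | 64% |
| 0.7, 0.7 SD | 79% | 85% | 81% |
| 0.85, 0.5 SD | 78% | 82% | 77% |
| 0.9, 0.4 SD | 77% | 80% | 75% |

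Baseline adjustment helps in every row. Four uninformative covariates cost 4 to 5 points here, and 2 to 3 points in a separate simulation that used minimised allocation (1,500 runs). They remove the gain at rho 0.85 and above.

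**If the factors are prognostic.** In that separate simulation, with the factors explaining 15% of the residual variance, power was:

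| rho | Mann–Whitney on change | ANCOVA, baseline only | ANCOVA, baseline + four factors |
|---|---|---|---|
| 0.5 | 67% | 81% | 83% |
| 0.7 | 73% | 83% | 86% |
| 0.85 | 75% | 81% | 83% |

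The Mann–Whitney test then rejected about 3.9% of the time under the null. It was slightly conservative, not inflated.

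**Scale.** With log-normal data and a non-prognostic set of factors, ANCOVA on the raw scale gave, for Mann–Whitney against ANCOVA:
- rho 0.5: 70% against 76%
- rho 0.7: 72% against 71%
- rho 0.85: 75% against 71%

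The advantage therefore shrinks or reverses on the wrong scale. In another simulation of log-normal data (log SD 0.4, effect 0.7 SD) with ANCOVA on the log scale, the figures were 47% against 68% at rho 0.5 and 68% against 85% at rho 0.7. Part of that gap comes from the transformation. The normal-data table is the like-for-like comparison of adjusted with unadjusted.

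**The case against.** The best defence is that this is a pilot trial with safety and tolerability as its primary endpoint and descriptive main analyses. Gait and cognition are secondary, and a rank test is a robust default across many outcomes in 40 people, some of them bounded or skewed. Under randomisation the change-score contrast is unbiased, since regression to the mean affects both arms equally in expectation. All of this stands, and it limits the weight of the point. It does not remove it, because this is the one between-group efficacy comparison the article names.

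A reader might infer more than the article supports:

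- **That baseline is ignored.** It is not. The change score uses it, with a slope fixed at 1.
- **That minimisation is wasted.** Balance on prognostic factors reduces the true variability of the contrast even without modelling. The unadjusted test only fails to credit this, which explains the 3.9% rejection rate.
- **That nothing usable for planning will be reported.** Means, medians, SDs and interquartile ranges are promised, and these serve sample-size work. What is not named is a between-group estimate with an interval. A fuller document might supply that, so it is a supporting remark.
- **That a five-covariate model is always better.** It is not, as the working shows.

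**Conclusion.** The point holds as a matter of efficiency. The stated test is less precise than a baseline-adjusted analysis of the same data, and its result moves with chance baseline imbalance. The direction is clear provided a suitable scale is used. The size is not known, because the article gives no pre–post correlation: the variance reduction runs from about a third at rho 0.3 to 2–5% at rho 0.9, and the simulated power gain from baseline adjustment alone runs from 14 points at rho 0.5 to 3 points at rho 0.9. These figures rest on assumed correlations, effects and distributions. Whether the four factors add or cost power depends on their prognostic value, which the article does not report. It would be wrong to conclude that the trial misses a power target, since none is set. This is a low-cost improvement to a secondary comparison.

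**What to change.** Replace the sentence on Mann–Whitney tests with wording to this effect:

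- For each gait and cognitive outcome, estimate the between-arm difference at 12 weeks by ANCOVA on the post value, with the baseline value of the same outcome as covariate, and report it with a 95% CI.
- State the scale in advance: for example log for gait-variability and reaction-time measures, and a rank-based analysis for bounded or badly skewed outcomes such as digit vigilance accuracy.
- Include age, sex, MoCA and MDS-UPDRS-III either in the model or in a pre-stated supporting analysis. Acknowledge a cost of about 2 to 5 power points if they are not prognostic and a gain if they are.
- Keep the Mann–Whitney test as a sensitivity analysis with a Hodges–Lehmann estimate and interval, and drop the description of it as a comparison of medians.

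The cost is analysis wording only. The baseline outcomes and the four factors are already collected.

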## Discussion

nVNS is a non-pharmacological neuromodulation intervention currently approved by the FDA for the acute and preventive treatment of most forms of primary headache and received a CE mark from the Medicines and Healthcare products Regulatory Agency (MHRA) for the treatment of primary headache, as adjunctive therapy to reduce symptoms of certain anxiety and depression conditions and to reduce symptoms of gastric motility disorders and irritable bowel syndrome. nVNS furthermore has some evidence in improving symptoms in conditions including fatigue and systemic inflammation [64] which are characteristic features of PD.

In PD, previous investigations have shown that single-dose nVNS [24, 65] may improve discrete gait characteristics. However, no formal investigation of the safety and tolerability of the device has been conducted, especially in a multi-dose nVNS trial. According to findings from a large meta-analysis that synthesised all reported adverse events from studies, the safety profile of vagal stimulation is excellent [34].

In this 24-week feasibility trial, we aim to generate clinical, digital and laboratory data to assess the safety, tolerability, feasibility, and potential effectiveness of domiciliary multi-dose nVNS in people with Parkinson’s. Further outcomes from this study include metrics needed for sample size calculations for future studies and evidence that improvement in gait, cognition and autonomic function is enhanced when nVNS is delivered repeatedly and whether this is sustained over time. Critically, these study outcomes will be used to provide input to a future larger multi-centre trial with benefits seen for patients within the next few years.

## Data Availability

Not applicable. Data will be pseudo-anonymised using a unique identification code assigned at the first assessment and entered to a secure data system on Newcastle University computers for analysis.

## Abbreviations

CANTAB: Cambridge neuropsychological test automated battery
CFS: Clinical frailty scale
CRT: Choice reaction time
DV: Digit vigilance
ECG: Electrocardiography
FACIT-Fatigue: Functional assessment of chronic illness therapy-fatigue
GCSI: Gastroparesis cardinal symptom index
GDS: Geriatric depression scale
HRV: Heart rate variability
LLFDI: Late-life function & disability instrument
MDS-UPDRS: Movement disorders society-unified parkinson's disease rating scale
MHRA: Medicines and healthcare products regulatory agency
nbM: Nucleus basalis of meynert
OTS: One touch stockings
PAL: Paired associative learning
PD: Parkinson's disease
PDQ-39: Parkinson's disease questionnaire-39
PwP: People with parkinson‘s
REC: Research ethics committee
SRT: Simple reaction time
TAU: Treatment as usual
TMT: Trail making test
VN: Vagus nerve
VNS: Vagus nerve stimulation
